## **Statistical Analysis Outline**

Linear and logistic mixed effects modelling are used to test the primary and secondary trial objectives (with the exclusion of the health economic analyses, which will be conducted by [name] and therefore not part of this analysis plan, as well as the hormone and immune function analyses which will be conducted by Professors [name] and [name]), which is the standard technique for analysing clinical trials.

For the primary and secondary trial objectives, 1-year follow-up is the short-term primary outcome time point (except for immune and hormone function for which the time-point is post-intervention), PTSD and MDD diagnoses are the primary outcome measures. Once completed, the 2-year PTSD and MDD diagnoses at 2-year follow-up are the long-term and main primary outcome time points.

Both repeated assessments and intervention arm are specified as categorical variables for reasons of flexibility in the modelling approach. Repeated assessments, intervention arm, their interaction effects, and baseline scores and covariates are estimated as fixed effects and random effects are estimated for time (level 1) nested within the participants (level 2). An unstructured variance-covariance matrix is used to model the error correlation structure within the participants.

Global comparisons for the main effect of intervention group and the interaction effects between time and intervention group are tested for primary and secondary trial objectives and further group comparisons are carried out if the global comparisons are significant. The hierarchy of the group comparisons reads as follows: 1) iCT-R versus Mind-Online, 2) iCT-R versus Standard Practice, and 3) Mind-Online versus Standard Practice. Site is introduced as a random effect in the analyses of the primary trial objectives. If non-significant, site will not be carried forward into further trial analyses.

Maximum Likelihood estimation is used. Assumptions for mixed effects modelling are tested and normality of residuals are confirmed for the outcome measures. If assumptions are violated, resampling approaches will be used.

Estimated/ adjusted mean differences and Cohen's d's are reported for continuous outcomes. Cohen's d's with standard deviation at baseline in the denominator are reported for the treatment effects from results of linear mixed effects models. Estimated/ adjusted odds ratios are reported for dichotomous outcomes together with absolute values. Confidence intervals are reported at the 95% level, two-sided.

Tertiary trial objectives to investigate any influences of baseline risk factors and predictors on iCT-R intervention effects on outcomes, such as PTSD or MDD diagnoses, psychological distress, or well-being, are tested using linear and logistic mixed effects models using the same analysis principles as for the primary and secondary trial objectives. The main effects of the respective baseline risk factors and predictors (time-invariant covariates) and the two-way interactions between each of those baseline predictors and time (categorical: post-intervention, 1-year follow-up; level 1) are analysed. Baseline scores of PTSD or MDD symptom severity, or psychological distress, or well-being are used as covariates.

In case of any significant interaction effects between time and baseline moderators, simple slope analyses are carried out to investigate the direction of any moderation effects. Further tertiary trial objectives to investigate whether changes in process measures, such as rumination, intrusive memories, and concrete thinking, from baseline to post-intervention in the iCT-R condition predict PTSD and MDD diagnoses at 1-year follow-up will be analysed using logistic regressions with difference scores from pre to post for the process measures and baseline scores of PTSD or MDD symptom severity as covariate.

CACE and sensitivity analyses are conducted for the primary trial objectives.

Results are reported in APA format.

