### 11.2 The Number of Participants

We plan to recruit 570 participants.

The risk of student paramedics developing full syndromal PTSD and MD over two years without intervention is 10% (1), and 25% if subsyndromal PTSD and MD that cause significant distress are included. We predict that our intervention will reduce the relative risk by 50%. Setting power at 80%,  $\alpha=.05$  and hypothesizing a reduction of relative risk of 50% gives an odds ratio of 0.429, which requires a total sample size of N=304 to show a risk reduction of 50% between the active and placebo intervention. Thus, each condition would require N=152. Since we have a third condition (no-training control), the total sample size required would be N=456. Allowing for a 20% rate of attrition, we will require a total sample size of N=570.

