#### **Timing of Final Analysis**

Originally, as stated in the published trial protocol ([name] et al., 2018), we had planned to analyse the trial data once the trial was finished at two year follow-up. However, the outbreak of the Covid pandemic may have added additional risk to the mental health of emergency workers and therefore, if iCT-R leads to improvement in emergency workers' mental health compared to Mind-Online or Standard Treatment, it would be beneficial to roll out the intervention as soon as possible. It has been discussed and agreed with the Trial Steering Committee that data could be analysed early, namely after completion of the 1-year follow-up period, if rates of PTSD and MDD diagnoses in the total sample at 1-year follow-up are higher than expected. At 1 year follow-up, in the total sample, rates of PTSD are 8.7% compared to 8.3% in non-intervention studies of this population [1] and the general population rate of 3%. Rates of depression are 15.8% compared to 10.6% in non-intervention longitudinal studies of this population [1] and the general population rate of 10.3%. Since

there are higher than expected rates of PTSD and MDD diagnoses at 1-year follow-up in the total sample we now plan to analyse data at 1-year follow-up. Two-year follow-up data (including sub-thresholds) will be analysed by including them into the 1-year outcome models once they have been completed.

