## **STATISTICAL PRINCIPLES**

### **Statistical Significance and Multiple Testing**

In the case of different scaling, continuous variables are standardized for the analysis. Global comparisons are tested and if significant, group comparisons are then carried out.

[name], [name], [name], [name], [name], [name], [name], [name], [name], [name], [name], & [name] Cognitive resilience training to prevent PTSD and MDD in paramedics: A randomised controlled trial.

If not specified otherwise, one or the other, main effects of intervention group or interaction effects between intervention group and time in favour of iCT-R, indicate intervention superiority.

All analyses will be carried out with a significance level of  $p < .05$ , two-sided.

No adjustments for multiple testing are made, as the primary trial objective is to evaluate any superiority in efficacy of the new resilience intervention compared to the existing online intervention (group comparison between these two groups of highest priority and directive hypothesis).

Confidence intervals are reported at the 95% level, two-sided.

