In case of any significant interaction effects between time and baseline moderators, simple slope analyses are carried out to investigate the direction of any moderation effects.

Further tertiary trial objectives to investigate whether changes (decrease) in process measures, such as rumination, intrusive memories, and increases in concrete thinking, from baseline to post-intervention in the iCT-R condition predict lack of PTSD or MDD diagnoses

[name], [name], [name], [name], [name], [name], [name], [name], [name], [name], [name], & [name] Cognitive resilience training to prevent PTSD and MDD in paramedics: A randomised controlled trial.

(versus presence of PTSD or MDD diagnoses) at 1-year follow-up are analysed using logistic regressions with difference scores from pre to post for the process measures and baseline scores of PTSD or MDD symptom severity as covariate.

CACE analysis:

A complier-average causal effect analysis (CACE) is used to test the influence of compliance on the intent-to-treat intervention effect of the primary trial objectives/ analyses. Magnitude of compliance will be defined as 1) number of online modules completed during the intervention, and 2) practice of tools. Based on these variables, trajectories of compliance are determined. CACE will then be compared with the intent-to-treat intervention effects resulting from the primary analyses and the results will be reported.

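### The SAP does not say whether PTSD and MDD diagnoses form one primary event or two, and the stated 80% power belongs to a broader single event

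*Combined protocol and SAP*

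**What the plan says.** **Sample size.** Protocol 11.2 gives one risk for the two disorders together: "The risk of student paramedics developing full syndromal PTSD and MD over two years without intervention is 10" per cent, "and 25% if subsyndromal PTSD and MD that cause significant distress are included". It assumes a 50% relative reduction and an odds ratio of 0.429, and arrives at 304 for two arms, 456 for three and 570 after 20% attrition. SAP 3.3 repeats the odds ratio and the totals, applies the 50% to PTSD and MDD diagnoses, and gives no base rate.

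**Primary outcome.** SAP 3.7 uses the plural: "PTSD and MDD diagnoses are the primary outcome measures". SAP 6.1 (Outcome Definitions) uses the singular for the same SCID-5 diagnoses. So does SAP 6.2 where it describes the group contrasts. SAP 6.6, in the Covid analyses, counts two measures for the primary objectives: the diagnoses as one, symptom severity as the other. The primary analysis paragraph in SAP 6.2 specifies logistic mixed models, in the plural, with both diagnoses as outcomes. It states no composite rule and no two-model rule.

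**Observed rates.** SAP 3.5 reports the diagnoses separately: "At 1 year follow-up, in the total sample, rates of PTSD are 8.7" per cent (8.3% in non-intervention studies), and depression is 15.8% (10.6%).

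**Error rate.** SAP 4.1 sets p < .05, two-sided, and makes no adjustment for multiple testing. Its reason is the priority of the iCT-R versus Mind-Online contrast; it does not mention having two diagnoses.

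**The concern.** The wording admits three primary events. Someone with depression and no PTSD is an event under an either-diagnosis rule, an event in one model and a non-event in the other under two separate models, and a non-event if both diagnoses are required. The choice sets the event rate and therefore the power, and the sample size was computed for only one such choice.

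With two models there is also no stated reading of a split result. If one positive diagnosis is enough, the error rate exceeds 5%. If both are needed, power cannot exceed that of the weaker test. Pooled rates were already known when this first SAP version was written, so the event should be fixed before the arms are compared.

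**Working it through.** **Inputs.** Two-sided 0.05 (SAP 4.1); "Setting power at 80" per cent and a 50% relative reduction (protocol 11.2); 152 analysable per arm; separate rates from SAP 3.5.

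**Formulas.** With p2 = p1/2 and m = (p1 + p2)/2:

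- n per arm = [1.960·√(2m(1−m)) + 0.842·√(p1(1−p1) + p2(1−p2))]² / (p1−p2)²
- power = Φ{[(p1−p2)·√n − 1.960·√(2m(1−m))] / √(p1(1−p1) + p2(1−p2))}

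**The plan's own figure.** At p1 = 0.25 and p2 = 0.125, m = 0.1875. The numerator is (1.960 × 0.5520 + 0.842 × 0.5449)² = 2.373; divided by 0.125² = 0.015625 this is 151.9, so 152 per arm and 304 in total. Power at 152 is 80.0% and the odds ratio is (0.125/0.875)/(0.25/0.75) = 0.429. Then 3 × 152 = 456 and 456/0.8 = 570. The figures reproduce exactly at 25%. At 10% the two-arm total would be 870, so the sizing event is the combined one that includes subsyndromal cases.

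**One substitution in full.** PTSD at 8.7%: p2 = 0.0435, m = 0.06525, √(2m(1−m)) = 0.3493, √(p1(1−p1) + p2(1−p2)) = 0.3479, √152 = 12.33. Power = Φ[(0.0435 × 12.33 − 1.960 × 0.3493)/0.3479] = Φ(−0.43) = 34%.

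**Scaling for pooled rates.** The 8.7% and 15.8% are averages over three arms. If iCT-R halves a risk r and the other two arms share r, the average is (r + r + r/2)/3 = 5r/6, so r is 1.2 times the pooled rate: 10.4% and 19.0%.

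**Either-diagnosis rate.** It lies between the larger single rate (complete overlap) and the sum (no overlap). Pooled: 15.8% to 24.5%, or 0.087 + 0.158 − 0.087 × 0.158 = 23.1% if independent. Non-intervention: 10.6% to 18.9%.

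| Event | Comparator rate | Power at 152 per arm |
|---|---|---|
| Sizing event, with subsyndromal cases | 25% | 80% |
| PTSD alone, non-intervention | 8.3% | 32% |
| PTSD alone, pooled 1-year | 8.7% | 34% |
| PTSD alone, pooled × 1.2 | 10.4% | 39% |
| MDD alone, non-intervention | 10.6% | 40% |
| MDD alone, pooled 1-year | 15.8% | 57% |
| MDD alone, pooled × 1.2 | 19.0% | 66% |
| Combined full diagnoses, protocol 11.2 | 10% | 38% |
| Either, non-intervention | 10.6% to 18.9% | 40% to 66% |
| Either, pooled 1-year | 15.8% to 24.5% | 57% to 79% (76% if independent) |
| Either, pooled × 1.2 | 19.0% to 29.4% | 66% to 87% |

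At the unscaled rates, separate tests would need two-arm totals of 1,062 and 1,010 for PTSD, and 816 and 524 for MDD, against 304.

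**Error rate.** If either diagnosis suffices and the two tests are independent, the chance of at least one false positive is 1 − 0.95² = 9.75%. Positive correlation between the tests would lower it.

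**The case against.** The strongest reply is that the SAP means one event. SAP 6.1, the contrasts paragraph of 6.2, and 6.6 all use the singular. SAP 6.2 writes of modelling either PTSD or MDD for symptom severity but not for diagnoses. Its plural models may only reflect the 1-year and 2-year analyses named in the same sentence. This stands as far as it goes: a reader might infer from SAP 3.7 that the trial commits to two separate primary tests, and the documents do not support so firm a reading. But the SAP does not commit to a composite either, so the definition is missing.

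A reader might also infer that the primary event changes between sections, because SAP 6.2 has an analysis of absence "versus presence of PTSD or MDD diagnoses) at 1-year follow-up". That is a tertiary process analysis in the iCT-R arm, and SAP 3.7 describes the same analysis with the other conjunction. It shows loose wording and does not alter the primary event. SAP 3.5 gives separate rates to justify early analysis; it defines no outcome.

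Two further points stand. Splitting the diagnoses is not the only source of the shortfall: the 25% includes subsyndromal cases, the SAP's primary outcome is SCID-5 diagnoses, and SAP 3.5 mentions sub-thresholds only for the 2-year data. And the sizing rate is a 2-year risk and the main primary time point is 2 years, while the SAP 3.5 figures are 1-year trial rates or external rates with no stated time frame.

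**Conclusion.** The primary event is undefined, and the stated 80% power applies only to a single combined event at 25%. Tested separately, neither diagnosis reaches 80% at any rate the documents give: 32% to 34% for PTSD and 40% to 57% for MDD, or 39% and 66% after the 1.2 scaling. Family-wise error could reach about 9.8% if either result counts.

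It is tempting to conclude that an either-diagnosis composite recovers the power. The documents do not support that. A composite of full diagnoses has 38% power at the protocol's 10%. At the SAP 3.5 rates the answer turns on the overlap between PTSD and MDD, which is not given; only the scaled rates with limited overlap pass 80%. The composite's case is that it matches the one-event sizing and removes the split result.

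These figures assume a common 50% reduction, 152 analysable per arm and the two-proportion method that reproduces the plan's own N. The adjusted repeated-measures model could differ somewhat. None of the SAP 3.5 figures is presented as a 2-year rate, so this is not the power of the 2-year analysis. The inputs also conflict: 10% for the two disorders together is lower than 10.6% for depression alone, cited to the same prospective study, so definitions or time frames must differ.

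**What to change.** In SAP 6.1 and 6.2, define the primary outcome as one binary variable per participant and visit: meets criteria for PTSD or MDD, either. State whether subsyndromal cases count; the protocol's primary objective and the 25% sizing rate include them. Fit one primary model and report PTSD and MDD separately as secondary component analyses. Align the wording of SAP 3.7 and 6.6. In SAP 3.3, restate the power with a base rate that matches the chosen event and time point, and show a range for overlap if it is unknown. If two primary outcomes are really intended, state instead whether one or both must succeed, give the multiplicity rule, and report power for each.

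The cost is SAP wording and one derived variable from SCID-5 interviews already scheduled; any subsyndromal rule must also be written down. There are two downsides: the composite pools two disorders, which the component analyses make visible, and the restated power may be less favourable than 80%.

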### 11.3 The Level of Statistical Significance

Significance levels were set at  $p < .05$ .

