## **Sample Size**

There are no interventions for emergency workers which target modifiable risk factors. Power calculation was approximated using the results of a study with a similar approach. Topper et al. (2017) found that an intervention targeting rumination reduced rates of depression in adolescents at 1-year follow-up by 57% compared to wait-list. We estimated that iCT-R, which also aims to reduce rumination, would reduce PTSD and MDD diagnoses by 50% in comparison to Mind-Online which has shown no change in rates of PTSD or MDD over time based on previous research. Setting power at 80%,  $\alpha = 0.05$  and hypothesising a reduction of relative risk of 50% results in an OR of 0.429 requires a total sample size of  $n = 304$  to show a risk reduction of 50% between iCT-R and Mind-Online. Therefore, each intervention arm requires  $n = 152$ . Including the third treatment arm, which is

Standard Practice, the total sample size required is  $n = 456$ . Allowing for 20% attrition, a total sample size of  $N = 570$  is required.

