## **Analysis Methods**

Analyses of the primary trial objectives:

To analyse any differences between the intervention arms in terms of effectiveness with regards to rates of PTSD and MDD diagnoses (SCID-5) at 1-year follow-up (short-term primary outcome time point) and at 2-years follow-up (long-term primary outcome time point once completed), intervention condition and the interaction between intervention time and

intervention group on rates of PTSD and MDD diagnoses, logistic mixed effects models with PTSD and MDD diagnoses as outcomes (short-term outcome 1-year follow-up data, long-term outcome 2-years follow-up once completed) are specified and analysed.

To analyse any differences between the intervention arms in terms of effectiveness with regards to PTSD symptom severity (PCL-5) or MDD symptom severity (PHQ-9) at 1-year follow-up (short-term primary outcome time point) and at 2-years follow-up (long-term primary outcome time point once completed), intervention condition (categorical; iCT-R versus Mind-Online versus Standard practice; level 2) and the interaction between intervention time (categorical; post-intervention, 6-months follow-up; 1-year-follow-up, 2-year follow-up, once completed; level 1) and intervention group on PTSD or MDD symptom severity, linear mixed effects models with either PTSD or MDD symptom severity as outcomes are specified and analysed.

Both repeated assessments and intervention arm are specified as categorical variables for reasons of flexibility in the modelling approach. Repeated assessments/ time, intervention arm, both their interaction effects, and baseline scores and covariates are estimated as fixed effects and random effects are estimated for time (level 1) nested within the participants (level 2). An unstructured variance-covariance matrix is used to model the error correlation structure within the participants. Estimation method is Maximum Likelihood. Normality of the residuals for the outcomes is confirmed visually.

Randomisation has been done by stratification by site, gender, and baseline PTSD symptom severity and MDD symptom severity. Therefore, baseline PTSD symptom severity and MDD symptom severity and randomisation factors are added as covariates in these models. Site is added as random factor in those models. If non-significant, they will not be carried forward into further analyses.

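### The SAP gives the logistic models for PTSD and MDD diagnoses a covariance specification that only linear models can carry; read literally, the size of the primary adjusted odds ratio is practically undetermined

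*Combined protocol and SAP*

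**What the plan says.** The SAP's Statistical Analysis Outline introduces linear and logistic mixed models together and then gives one specification for both. Time and arm are categorical, random effects are estimated for time within participant, estimation is by maximum likelihood, and "An unstructured variance-covariance matrix is used to model the error correlation structure within the participants". Analysis Methods specifies "logistic mixed effects models with PTSD and MDD diagnoses as outcomes" for the primary objective, then a linear model for PCL-5 and PHQ-9, and then repeats the same random-effect and error-matrix text. Neither section gives a separate rule for binary data.

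Under Outcome Definitions, diagnoses are assessed before and after the intervention and at 1 and 2 years, but not at 6 months. Adjusted odds ratios are reported with absolute numbers and percentages. The SAP does not say whether the odds ratio is participant-specific or marginal. It gives no fallback for a singular or non-converged fit, only resampling if model assumptions are violated.

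For planning, protocol 11.2 takes a two-year risk of "25% if subsyndromal PTSD and MD that cause significant distress are included", halves it, and says this "gives an odds ratio of 0.429". The SAP's Sample Size section uses the same value.

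**The concern.** In a linear mixed model an unstructured matrix across visits is routine, because each visit has its own residual variance and each pair of visits its own covariance. A yes/no diagnosis has no such free matrix: once its probability is set, so is its variance. Carried over to the logistic models, the text asks for covariance parameters that a few binary results per person can barely inform.

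The random-effect variance also sets the scale of a conditional odds ratio. If the data cannot fix the variance, they cannot fix the size of the odds ratio, even when they show clearly that the arms differ. That odds ratio is the SAP's modelled effect measure for its primary outcome. If the fit fails or is singular, the analyst must choose another structure after seeing the data, on the primary endpoint.

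**Working it through.** **1. The plan's own figures.** Inputs (protocol 11.2; SAP Sample Size and Statistical Significance and Multiple Testing): risks 25% and 12.5%, two-sided 5%, power 80%, 20% attrition.

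- Odds ratio = (0.125/0.875)/(0.25/0.75) = 0.429.
- n per arm = [1.96√(2×0.1875×0.8125) + 0.8416√(0.25×0.75 + 0.125×0.875)]² / 0.125² = 151.9, so 152.
- 2×152 = 304; 3×152 = 456; 456/0.8 = 570.

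All reproduce. The 0.429 is a marginal odds ratio, computed from two population risks.

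**2. Counting parameters.** I take baseline as a covariate, as the SAP does. The time levels of the diagnosis model are not listed, so the visit count is inferred from Outcome Definitions and the schedule. With T visits and one random effect per visit, the covariance matrix has T(T+1)/2 parameters, against T(T−1)/2 pairwise associations per arm.

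- 1-year analysis, T = 2: 3 parameters, 1 association.
- 2-year analysis, T = 3: 6 parameters, 3 pairwise associations.

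Arm-by-time fixed effects already absorb every arm-by-visit rate. If a second normal "error" matrix is added on the logit scale, only the sum of the two matrices enters the likelihood, so the two cannot be separated at all. Without it, the variances are informed only weakly, through the shape of the logistic-normal distribution.

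**3. How flat the likelihood is.** From the documents: 152 per arm, three arms. Taken from the planning risks but moved to 1 year for illustration: 12.5% (iCT-R) and 25% (both other arms). Assumed: post-intervention risks 5% and 10%, true SD 2 at both visits, correlation 0.6. For each fixed SD (equal at both visits), the fixed effects and the correlation were re-fitted to the expected data by Gauss-Hermite quadrature.

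| SD | Deviance loss | Conditional 1-year OR | Implied marginal OR |
|---|---|---|---|
| 1.3 | 0.0022 | 0.350 | 0.4285 |
| 1.5 | 0.0009 | 0.330 | 0.4285 |
| 2 | 0 | 0.279 | 0.4286 |
| 3 | 0.0007 | 0.189 | 0.4287 |
| 4 | 0.0013 | 0.124 | 0.4287 |

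A loss of 3.84 would be needed to reject an SD at 5%.

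**4. What moves and what does not.** The likelihood-ratio statistic for any arm effect is 12.34 in every row. The 1-year Wald z, with the SD held fixed, is −2.77 to −2.78. The interval moves with the odds ratio:

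- SD 1.3: SE = ln(0.350)/(−2.77) = 0.379, so the 95% CI is exp(−1.050 ± 1.96×0.379) = 0.17 to 0.74.
- SD 4: SE = ln(0.124)/(−2.78) = 0.751, so the 95% CI is exp(−2.087 ± 1.96×0.751) = 0.03 to 0.54.

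**5. Other settings** (assumed true SD 2, correlation 0.6).

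- Three visits, post-intervention risks 10% and 15%: SDs 2, 3 and 4 lose at most 0.007; conditional OR 0.279, 0.189, 0.124.
- Two visits with a continuous baseline covariate (assumed coefficient 1): SDs 1.5 to 4 lose at most 0.010; OR 0.332 to 0.125.
- The same with 1-year risks of 8.6% and 16.6%, nearer the pooled rates in Timing of Final Analysis (PTSD 8.7%, depression 15.8%): OR 0.365 to 0.156, again losing at most 0.010.

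**6. A participant random intercept instead** (assumed true SD 1.5, post-intervention risks 10% and 15%).

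| SD | Loss, 2 visits | Loss, 3 visits |
|---|---|---|
| 1 | 3.77 | 9.25 |
| 1.5 | 0 | 0 |
| 2 | 3.09 | 6.65 |
| 3 | 20.69 | 41.75 |

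This model is identified. It is still on another scale: with marginal risks held at 12.5% and 25%, the conditional OR is 0.429, 0.379, 0.279 and 0.189 at SD 0, 1, 2 and 3.

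**The case against.** The strongest reply is that the literal reading is uncharitable. Random effects for time within participants may simply mean repeated measures clustered in people, that is, a random intercept. In Analysis Methods the error-matrix sentence follows the linear symptom models and precedes a check of residual normality, and the SAP names both lme4 and nlme. This stands as a possible reading. But then the word "unstructured" means nothing for diagnoses, and two competent analysts could fit different primary models from the same text.

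Three stronger conclusions are tempting, and the documents do not support them.

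- **That the superiority decision is arbitrary.** The SAP decides superiority by significance, and the test statistics were stable over the SD grid. Percentages by arm are reported as well.
- **That the reported effect will be exaggerated.** The table traces the likelihood along equal SDs; it does not predict a fitted value. In five simulated trials fitted literally in lme4, four gave convergence or identifiability warnings. The 1-year odds ratio was close or equal to the raw marginal one in four and nearer 1 in the fifth (0.901 against 0.643). The run is small, but it shows no exaggeration.
- **That the variance problem explains a gap from 0.429, or undermines the sample size.** Any logistic mixed model with SD above 0 gives a conditional odds ratio further from 1 than the marginal one for the same risks, even when fully identified. The planning value is correct on its own scale, and the SAP nowhere compares the estimate with it.

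**Conclusion.** The specification is wrong as written for the primary binary outcome. An unstructured error matrix does not exist for it, and one random effect per visit leaves the variance practically undetermined. Without a second matrix the failure is practical, not formal. In the main illustration the odds ratio varies about threefold (0.350/0.124 = 2.8) with no visible change in fit, and its interval moves with it. The marginal risks and the tests of arm effect are essentially unaffected.

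The exact figures rest on the assumed SD, correlation and post-intervention risks, and on using two-year planning risks, which include subsyndromal cases, at 1 year. The flatness itself persisted with three visits, with a baseline covariate, and at rates nearer those observed. The participant-specific versus marginal scale is a separate omission, and it would remain under an identified mixed model.

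**What to change.** Before the diagnosis models are run, amend Statistical Analysis Outline and Analysis Methods as follows:

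- Limit the unstructured error matrix to the linear models.
- For diagnoses, name one identified analysis that keeps arm, time and arm-by-time, with baseline PCL-5 and PHQ-9 and the randomisation factors. It can be a logistic model with a participant random intercept, or a marginal logistic model (GEE), where an unstructured working correlation is legitimate.
- List the time levels of the diagnosis model.
- State whether the odds ratio is participant-specific or marginal. At each primary time point, report the standardised (marginal) risk difference and odds ratio with 95% CI.
- Pre-specify what is fitted if the model is singular or does not converge.

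The cost is SAP wording and modest analysis work, with no new data. If GEE is chosen, missing SCIDs need the imputation that the SAP already lists under Sensitivity Analysis, with its method spelled out, because GEE alone does not handle data missing at random. The random-intercept route avoids that step, but needs standardisation to give marginal effects.
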